##### Quadriceps muscle volume

Quadriceps muscle volume will be obtained via magnetic resonance imaging (MRI) scans performed with a 0.25-Tesla Musculoskeletal MRI system (Esaote G-Scan Brio, Genoa, Italy) to acquire contiguous transverse T-1 weighted spin echo image slices in the thigh region with a slice thickness of 10 mm and an inter-slice distance of 10 mm. The isocenter will be positioned at mid-thigh, midway between the patella and the inguinal crease, and the subjects will be supine. Images will be transferred to a computer for calculation of quadriceps anatomical cross-sectional area (CSA). Beginning with the slide with the first discernable visual of the rectus femoris and including the subsequent four proximal slides, quadriceps muscle area will be traced using a polygon tool, excluding bone, as well as fat tissue surrounding the muscles (MIPAV version 7.3.0). Intramuscular fat will then be subtracted by applying a shading correction to each slide, determining average voxel density and standard deviation voxel density from a sample of the lightest area of fat tissue, computing a cutoff value at three standard deviations darker than the sample voxel density, and excluding all pixels with a voxel density at or below the computed value. Pre- and post-intervention slides will be displayed simultaneously, and slides will be visually compared to ensure that tracing patterns are identical and that the same structures are excluded (i.e., neurovascular bundle, intermuscular fat) on both slides before CSA values are recorded. This process will be completed for each analyzed slide, resulting in five measures of quadriceps CSA with intermuscular and intramuscular fat excluded for both pre and post time points. Muscle volume will then be calculated using the Cavalieri method [MV = T (A_1_ + A_2_ + A_3_ + A_4_ + A_5_)], where MV = muscle volume, T = the known distance between slices, and A = area (57). Quadriceps muscle volume will be recorded at baseline and post-intervention, and percent change from baseline will be used for analysis.

#### Secondary Outcomes

##### Knee extensor isometric strength

Maximal isometric force production will be measured via three maximal voluntary contractions (MVCs) of the knee extensors while the subject is positioned in the Biodex Dynamometer as described above, with the lever arm immobilized at 90° of knee flexion. The subject will be instructed to gradually increase force for the first second, and then exert maximal effort for ~3–4 s. The subject will perform three MVCs with a 30–60 s rest period between contractions. Verbal encouragement will be provided during each trial. The time-series torque signal will be collected at 500 Hz by a Biopac MP150 system (Biopac Systems Inc., Santa Barbara, CA, USA). The trial with the highest value will be recorded at baseline and post-intervention, and percent change from baseline will be used for analysis.

##### Knee extensor isokinetic fatigue

Fatigue resistance of the knee extensors will be measured with the subject positioned in the Biodex dynamometer as described above. Subjects will be asked to perform a series of isokinetic leg extensions at 120°/s (the flexion component will be passive at a speed of 240°/s). First, study subjects will perform three isokinetic extensions recorded as pre-fatigue peak torque values. Next, study subjects will be given 3 min of rest before beginning the fatigue portion of the test. For the fatigue test, subjects will perform 120 consecutive maximal isokinetic leg extension contractions (test time ~4-min). Peak force for each of the 120 contractions will be summed to calculate total work output and will be recorded at baseline and post-intervention, and change from baseline will be used for analysis. The subject will be verbally encouraged throughout the test. Lastly, post-fatigue peak torque will be assed at 2, 5, and 10 min after the completion of the fatigue test. For all fatigue measurement, the time-series torque signal will be collected at 500 Hz by a Biopac MP150 system (Biopac Systems Inc., Santa Barbara, CA, USA). Average torque of three contractions at each of the post-fatigue timepoints will be recorded and expressed relative to the pre-fatigue torque at baseline and post-intervention, and percent change from baseline will be used for analysis.

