### Outcome Measures

#### Primary Outcomes

##### Knee extensor isokinetic power

Maximal isokinetic power will be measured from the knee extensors. Peak torque will be recorded from the non-dominant leg using a Biodex System 4 Dynamometer (Biodex Medical Systems, Inc., Shirley, NY). The subject's leg will be immobilized against the lever arm with the distal end of the lever arm secured three inches superior to the medial malleolus. The axis of the lever arm will be centered at the lateral knee joint and knee range of motion will be obtained by having the subject extend their knee as far as possible against the lever arm. The maximal knee extension angle will be recorded, and the knee extension limit will be set 10° less than the maximal knee extension angle. The subject will then relax to allow the leg to return to neutral position and the knee flexion limit will be set at 80° of knee flexion. The speed of the lever arm will be set at 60°/s for both extension and flexion. The subject will then extend the knee with maximal effort until they reach the knee extension limit, and then immediately flex the knee with maximal effort until they reach the knee flexion limit. The time-series torque signal will be collected at 500 Hz by a Biopac MP150 system (Biopac Systems Inc., Santa Barbara, CA, USA). The subject will complete six isokinetic trials, with 30 s rest between trials. The average of the three highest peak torque values for both extension and flexion will be recorded at baseline and post-intervention, and percent change from baseline will be used for analysis.

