## Anticipated Results

### The Dual-Benefits Hypothesis

The HIIT group will see improvements in endurance measures (VO_2_max, 6-min walk distance, isokinetic fatigue) equal to the MICT group and greater than the RT group, and improvements in muscular characteristics (isokinetic power, MVC, thigh muscle volume, VRFD, TRFD, voluntary activation) equal to the RT group and greater than the MICT group.

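### The fatigue-test total is a sum of peak torques rather than work and rises with strength, so a strength gain in RT or HIIT could be read as an endurance gain

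*Protocol article*

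**What the plan says.** All references are to the protocol article.

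- **Aim.** The section on knee extensor isokinetic fatigue, a secondary outcome, opens with: "Fatigue resistance of the knee extensors will be measured".
- **Test.** Three extensions give the pre-fatigue peak torque. After 3 min of rest the participant performs "120 consecutive maximal isokinetic leg extension contractions (test time ~4-min". Torque is recorded at 500 Hz throughout.
- **First result.** "Peak force for each of the 120 contractions will be summed to calculate total work output". The change from baseline in this sum is analysed, and no scaling to pre-fatigue torque is described.
- **Second result.** Mean torque of three contractions at 2, 5 and 10 min after the test is divided by pre-fatigue torque and analysed as percent change.
- **Role.** Under The Dual-Benefits Hypothesis, HIIT is expected to show "improvements in endurance measures (VO_2_max, 6-min walk distance, isokinetic fatigue) equal to the MICT group and greater than the RT group". HIIT is also expected to match RT and exceed MICT on muscular characteristics, including isokinetic power. The hypothesis does not say which of the two fatigue results it means.
- **Scale.** Statistical Methods gives percentage change for isokinetic fatigue, while the fatigue section gives plain change for the sum.
- **Speeds and range.** The fatigue section specifies "isokinetic leg extensions at 120°/s (the flexion component will be passive at a speed of 240°/s", with the participant positioned as for the power test. There, "the knee extension limit will be set 10° less than the maximal knee extension angle" and "the knee flexion limit will be set at 80° of knee flexion".

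**The concern.** Mechanical work in a contraction is torque integrated over the angle travelled. A peak is one point on that curve, so adding 120 peaks gives a quantity that is not work and takes no account of torque lost away from the peak.

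The larger issue is interpretation. A test introduced as measuring fatigue resistance yields a score that contains the participant's strength as a multiplier. RT trains knee extension in every session (Table 4), and HIIT is itself predicted to gain as much power as RT. If the sum is taken as the endurance result, a participant who becomes stronger and fatigues exactly as before is credited with better endurance. That blurs the contrast between muscular and endurance adaptation that the trial is designed to show.

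Separately, the stated duration does not follow from the stated speeds and range.

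**Working it through.** **1. Dependence on strength.** Let P be initial peak torque and f(i) the fraction of P kept at contraction i. The score is S = P × Σ f(i). If P becomes P × (1 + g) and the f(i) do not change, S becomes S × (1 + g). Gains of 5%, 10% and 20% therefore raise S by 5%, 10% and 20%, with no change in relative fatigue. Percentage change does not remove this, and neither does plain change.

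**2. What the sum would show if the hypothesis were true.** The article gives no torque or decline data, so these inputs are assumed. Baseline falls linearly from 100 to 40 N·m. Strength rises 15% in RT and HIIT. The decline stops at 50% of the start in MICT and HIIT. For a linear decline, S = 120 × (start + end)/2.

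| Case | Start to end, N·m | S | Change | % change | S/(120 × start) | % change in index |
|---|---|---|---|---|---|---|
| Baseline | 100 to 40 | 120 × 70 = 8,400 | – | – | 0.70 | – |
| RT | 115 to 46 | 120 × 80.5 = 9,660 | +1,260 | +15.0 | 0.70 | 0 |
| MICT | 100 to 50 | 120 × 75 = 9,000 | +600 | +7.1 | 0.75 | +7.1 |
| HIIT | 115 to 57.5 | 120 × 86.25 = 10,350 | +1,950 | +23.2 | 0.75 | +7.1 |

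The prediction is HIIT equal to MICT and both above RT. The sum shows HIIT above RT above MICT. The index shows the predicted pattern.

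**3. The sum also responds to fatigue.** Assume instead f(i) = p + (1 − p) × exp(−i/30) for i = 0 to 119, with plateau p of 0.3, 0.4 or 0.5.
- Plateau 5 points higher, strength unchanged: S rises 7.9%, 6.8% and 6.0%.
- Strength up 10%, absolute plateau unchanged (relative fatigue is then worse): S rises 5.3%, 4.5% and 4.0%.

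In step 2, if MICT fell only to 65%, its sum would be 120 × 82.5 = 9,900, above RT at 9,660. The RT–MICT ordering changes where (100 + end)/2 = 80.5, that is, at a final torque of 61%.

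**4. Sum of peaks against work.** Over 70° (1.22 rad), a flat torque curve gives 1.22 J of work per N·m of peak, and a half-sine gives 1.22 × 2/π = 0.78 J. The sum is proportional to work only if range and curve shape stay the same across contractions and visits.

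**5. Duration (separate point).** The stated figure is about 4 min for 120 contractions, or 240/120 = 2.0 s each. I assume that the power-test range carries over and that full extension is 0°, so the range is 80° − 10° = 70°.
- Cycle = 70/120 + 70/240 = 0.583 + 0.292 = 0.875 s. Total = 120 × 0.875 = 105 s.
- Ranges of 60° and 100° give 90 s and 150 s.
- Reaching 240 s needs a range of 2.0/(1/120 + 1/240) = 160°, or at 70° a pause of 2.0 − 0.875 = 1.125 s per contraction.
- Extension takes 0.583/0.875 = 67% of each cycle if continuous, and 0.583/2.0 = 29% if spread over 4 min.

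The stated 4 min is not reproduced from the stated speeds alone.

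**The case against.** **A strength-independent result is already planned.** The torque at 2, 5 and 10 min is divided by pre-fatigue torque, and strength is measured separately as isokinetic power and isometric strength, so a pure strength gain would be visible. This stands in part. The normalised values begin 2 min after the last contraction, so they partly reflect recovery rather than decline during the test. The hypothesis also does not name them as the endurance outcome.

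**Absolute output is a legitimate construct.** Total output over a fixed number of maximal contractions is a usable measure of absolute muscular endurance. This stands, and it is a reason to keep the total, but under a description that acknowledges its dependence on strength.

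**The label may be harmless.** With constant range and curve shape, the factor linking summed peaks to work cancels in percentage change. This stands as far as it goes, but the article does not establish that constancy, and strength dependence remains even for true work.

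**HIIT above RT survives.** In the example, HIIT scores +23% against +15% for RT. That is correct. What fails is HIIT equal to MICT, and with it the implied MICT above RT.

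**Stronger readings that do not hold.** A reader might infer that the sum mainly tracks strength and that RT gains would be reported as endurance. Without torque or decline data this cannot be shown, and step 3 shows that the sum mixes both influences. A reader might also treat the duration mismatch as part of the same fault. It is not: a short pause between consecutive contractions would explain it, and it does not cause the misreading of RT.

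**Conclusion.** The point holds in a limited form. The sum is mislabelled as work and is unscaled. Its proportional rise with strength at an unchanged relative fatigue curve is algebra and needs no assumption. The sizes of +23%, +7% and +15%, against +7%, +7% and 0% for the index, rest on the assumed 15% strength gain and linear declines to 40% or 50%. They illustrate what could happen and do not forecast it. The conclusion is that a strength gain in RT or HIIT could be read as an endurance gain, and that the sum would not show HIIT equal to MICT even if the hypothesis were fully true.

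This is a secondary outcome in a proof-of-concept trial, and neither the primary outcomes nor the sample size depend on it. It is still worth correcting because the outcome is named in the trial's central hypothesis.

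The duration mismatch (about 105 s at an assumed 70°, 90–150 s over 60–100°, against about 4 min) is a minor and separate reporting gap.

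**What to change.** 1. Compute work per contraction by integrating the recorded 500 Hz torque over angle at 120°/s. If that is not done, rename the score summed peak torque.
2. Add a within-test index: total work over the 120 contractions divided by (120 × mean work of the three pre-fatigue contractions). Name it as the fatigue measure for the endurance part of the dual-benefits hypothesis.
3. Keep the unscaled total, described as absolute output that depends on strength.
4. Reconcile plain change (fatigue section) with percentage change (Statistical Methods) for this outcome.
5. As a minor addition, state the range and the pause or cadence that reconcile the speeds with the 4 min, and keep them the same at both visits.

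The cost is some re-processing of a signal already being recorded and a few lines of text; no new test is needed. The downside is that a ratio with three contractions in its denominator will be somewhat noisier than the raw total, which is a further reason to report both.

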##### Six-minute walk distance

A 6-min walk distance test will be performed in a 30-meter hallway marked off with cones at either end, and distance marked every three meters. The subject will start at the end of the hallway (starting cone) and be instructed to walk as quickly as they can for 6 min. They will walk toward the end of the hallway, around the second cone, and then back toward the starting cone. The subject will complete as many laps as possible within 6 min, rounding the cones each lap. Subjects will be given feedback on elapsed/remaining time every 30 s, and encouraged to continue walking as quickly as possible. Distance covered in 6 min will be recorded to the nearest meter at baseline and post-intervention, and change from baseline will be used for analysis.

##### Body composition

Total body fat mass will be obtained via whole-body dual-energy X-ray absorptiometry (DXA) scans (Hologic Discovery QDR model Series, Waltham, MA, USA) using the system's software package (Hologic APEX, Version 4.0.2). Subjects will be scanned at the same time of day pre- and post-intervention and will be encouraged to maintain a similar sleeping and eating schedule for both scans. Subjects will be advised to report to the laboratory in a hydrated state and will be given scrubs to wear during the scan. They will also be given the opportunity to use the restroom prior to the scan. Care will be taken to follow The International Society for Clinical Densitometry guidelines for positioning during the scan (58). Total body fat mass will be recorded at baseline and post-intervention, and percent change from baseline will be used for analysis.

#### Other Outcomes

##### Knee extensor voluntary rate of force development (VRFD)

VRFD of the knee extensors will be measured with the subject positioned in the Biodex Dynamometer as described above with the lever arm set to 90° of knee flexion. The subject will extend the knee into the immobilized lever arm with maximal effort over ~500 ms, then immediately relax. The process will be explained to the subject so they understand that they are to produce as much force as possible, as quickly as possible, and then to relax (e.g., pretend you are kicking a tire as hard as you can). The time-series torque signal will be collected at 500 Hz by a Biopac MP150 system (Biopac Systems Inc., Santa Barbara, CA, USA). The trial with the highest VRFD (slope of force tracing between 10 and 90% of maximal force) will be calculated at baseline and post-intervention, and change from baseline will be used for analysis.

##### Twitch-evoked rate of force development (TRFD) and voluntary activation

TRFD and voluntary activation of the knee extensors will be obtained with the subject positioned in the Biodex dynamometer as described above with the lever arm set to at 90° of knee flexion. A surface stimulating electrode will be placed on the distal motor point of the vastus medialis and another on the proximal motor point of the vastus lateralis. Single pulses of incrementally increasing current will be delivered via a Digitimer DS7AH constant current stimulator (Digitimer Ltd., Hertfordshire, UK) until twitch force plateaus. The time-series torque signal will be collected at 500 Hz by a Biopac MP150 system (Biopac Systems Inc., Santa Barbara, CA, USA). TRFD (slope of the twitch response between 10 and 90% of maximal force) at maximal stimulation intensity will be calculated at baseline and post-intervention, and change from baseline will be used for analysis. Subjects will then perform two MVCs separated by 2 min, and during the MVC a doublet will be delivered at maximal intensity (intensity at which twitch force plateaus), followed by a second doublet delivered to resting muscle. Voluntary activation is expressed as [1–(doublet force during MVC/doublet force during relaxation)] ^*^ 100. The time-series torque signal will be collected at 500 Hz by a Biopac MP150 system (Biopac Systems Inc., Santa Barbara, CA, USA). The subject will perform two voluntary activation trials, and the average of the two measures will be recorded at baseline and post-intervention, and change from baseline will be used for analysis.

##### 4-square step test (4SST)

The 4SST is a test that challenges motor planning and initiation as well as motor sequencing and recall (59, 60). A four-foot by four-foot square will be marked with athletic tape and split into quadrants (Figure 2). The subjects will start in square 1, facing square 2. The subject then steps forward into square 2, laterally to square 3, backwards to square 4, laterally to square 1, laterally to square 4, forwards to square 3, laterally to square 2, and backwards to square 1, facing the same direction throughout the entire sequence. Subjects must place both feet in the specified quadrant before they can move into the next square, and must have at least one foot on the ground at all times. The test will be timed with a stop watch to the nearest 0.01 s. When the subject is ready the investigator will say “ready, set, go.” The timer will begin at “Go” and stopped when the subject has placed both feet back in square 1 after completing a clockwise and counter-clockwise cycle. The subject will perform two trials with 30 s rest between trials, and the fastest will be recorded at baseline and post-intervention. Change from baseline will be used for analysis.

**Figure 2 F2:**
[figure not shown]
4SST setup. The subject starts in square 1 facing square 2. The subject faces the same direction as they step into squares 2, 3, 4, 1, 4, 3, 2, and then 1.

##### Stair climb power

Stair climb power will be calculated as [power = force x velocity] where force = body mass in kilograms x acceleration due to gravity, and velocity = cumulative stair height/stair climb time. The subject will be weighed to the nearest pound, and free weights equivalent to 20% of their body weight will be distributed evenly into two canvas bags. The bags will be set aside for later weighted stair climb testing. The subject will stand at the bottom of a flight of eight stairs (each stair 7″ in height) with feet together. The subject will then be instructed to safely climb the stairs as quickly as possible without skipping any stairs, maintaining at least one foot on a stair at all times. The subject will also be instructed that they may use the handrails if necessary for safety purposes. The test will be timed with a stop watch to the nearest 0.01 s. When the subject is ready the investigator will say “ready, set, go.” The timer will begin at “Go” and stopped when the subject's first foot makes contact with the eighth stair. The subject will perform two trials, and the fastest will be recorded at baseline and post-intervention. Stair climb power will be calculated as described above, and change from baseline will be used for analysis. The subject will repeat the test while carrying the weighted bags equivalent to 20% of their body weight, one bag in each hand. The subject will perform two trials and the fastest will be recorded at baseline and post-intervention. Stair climb power will be calculated as described above, and change from baseline will be used for analysis. 30–60 s rest will be allowed between each trial.

##### Grip strength

Maximal grip strength will be obtained with a Jamar hydraulic grip strength dynamometer (Performance Health, LLC, Akron, OH USA). Handle position of the dynamometer will be standardized at position II (61, 62). Hand dominance will be determined by asking the subject if they were right-handed or left-handed. The dominant hand will be tested first. The subject will be seated with the shoulder in neutral position and the elbow unsupported and flexed to 90° with the forearm and wrist in neutral position (61). The subject will squeeze the dynamometer handle as hard as possible for 3 s. Maximal force will be recorded in kg. The subject will perform three trials with each hand, and 15 s rest will be allowed between trials. Average force of the three trials for each hand will be recorded at baseline and post-intervention, and change from baseline will be used for analysis.

### Exercise Intervention

Each subject will perform their prescribed exercise three times per week for 12 weeks. Time between visits will generally be 48–72 h, but may range from 24 to 96 h to meet the demands of the subject's schedule. Subjects may be allowed to exercise on consecutive days one time per week, but must have at least 48 h before a third exercise session is completed (for example, Monday, Tuesday, Thursday is acceptable, but Monday, Tuesday, Wednesday is not). Prior to each exercise session an exercise supervisor will perform a brief medical safety check. If the subject reports changes in health status that are concerning, has abnormal vital signs (blood pressure readings that exceed 170 mmHg for systolic blood pressure or 100 mmHg for diastolic blood pressure), or has changed medications/dosage, they will not be allowed to continue exercising until the study physician has reviewed the changes and clears the subject. After the medical safety check, the subject will perform a 5-min warm-up on the stationary bike at a low intensity (i.e., output 50% or less of their maximal output during the GXT). After the subject has completed the prescribed exercise for the day they will perform a 5-min cooldown at a low intensity on the stationary bicycle. For the RT and MICT exercise protocols we will employ a pragmatic trial design that follow the recommendations set forth by the ACSM, but that are not necessarily matched by time. There are currently no recommendations for HIIT in older adults, and the exercise sessions are shorter in duration due to the high-intensity nature.

